### Research collaboration and partnerships

This project involves collaboration between different research teams across Australia. A Memorandum of Understanding (MOU) was agreed upon by chief investigators of the respective studies prior to the commencement of this project, according to cohort-specific governance processes, including Aboriginal and Torres Strait Islander community consultation and approval. The MOU specifies how data will be shared, stored, and handled between parties involved. It also details acknowledgments of researchers involved in the original cohort studies in any future publications or presentations. The Statistical Analysis Plan for this study was registered on the public platform Open Science Framework (https://osf.io/jv6sx/) prior to data sharing. Regular meetings with the research data leads will occur every two to three months to update our collaborators on progress of the study.

### Ethics

The KHAP, KGOW and TSDP studies all adhere to the Australian National Health and Medical Research Council (NHMRC) guidelines for ethical conduct for research involving Aboriginal and Torres Strait Islander People and communities. All studies have ethics approval from local and Aboriginal Health and Medical Research Councils. This project to harmonise these landmark studies has received ethics approval from the Aboriginal Health and Medical Research Council (AHMRC) 1362/18 & 1445/18; Western Australian Aboriginal Health Ethics Committee (WAAHEC) HREC no. 858; University of Melbourne Project ID 12,140 ; the Far North Queensland Human Research Ethics Committee HREC/2020/QCH/63,123–1432 and James Cook University H9079. The most important risk for this project involves participant confidentiality in the process of data sharing. Breach of confidentiality may lead to a lack of respect for research organisations and affect relationships with Aboriginal and Torres Strait Islander communities in the future. To ensure that this does not occur, we have specified in our ethics applications and MOU to share only de-identified data that will be stored on a secure, password-protected server, accessible only to research leads. This also means that any reporting or feedback of data and results will be in aggregate form without identification of individual participants. Our project governance structure with consultation from Indigenous governance groups also ensures that this research is in keeping with the values of the Aboriginal and Torres Strait participants and that outcomes are translated back to benefit community.

### Project governance

This research is currently embedded in the Let’s CHAT (Community Health Approaches To) Dementia in Aboriginal and Torres Strait Islander Communities project [21]. When Let’s CHAT comes to completion, governance will be transferred and provided under the auspices of the recently established On TRACK (Teaching, Research And Community Knowledges) national research program. On TRACK is a NHMRC-funded Centre for Research Excellence (CRE) collaboration, which aims to promote brain health and optimise detection of dementia and cognitive impairment in older Aboriginal and Torres Strait Islander peoples through engagement with Aboriginal primary health care services and adheres to the key principles for ethical conduct in research with Aboriginal and Torres Strait Islander peoples based on NHMRC and AHMRC guidelines [22, 23].

The harmonisation of existing cohort data does not directly involve partnership with Aboriginal Community Controlled Health Services. Aboriginal and Torres Strait Islander governance is achieved through an Indigenous Reference Group (IRG) whose members are involved through the course of the project and are “representative of the group being studied and have knowledge or experience of the research matter” [22]. In its conceptualisation, this project has the support of the Let’s CHAT Dementia IRG and the KGOWS Steering Committee. The Let’s CHAT IRG comprises Elders and research team members with links to communities in Western Australia and the Torres Strait. The KGOWS Steering Committee is led by Aboriginal researchers who were involved in the KGOW studies, in conjunction with representatives from each of the partnering Aboriginal communities and independent Aboriginal and Torres Strait Islander members with expertise in brain health and ageing. The TSDPS was also governed by an Indigenous Knowledge Circle with members continuing to provide oversight of ongoing Torres Strait studies conducted by the Healthy Ageing Research Team (HART). Many members of the Let’s CHAT IRG have elected to continue as members of the On TRACK IRG and will provide ongoing governance for this project. This group will comprise of at least six Aboriginal and Torres Strait Islander members who will meet three times a year. In addition to annual project progress reports submitted to the ethic committees, presentations to the IRG will occur during these meetings. This will ensure that Indigenous governance groups are involved in interpretation of the research results and plans for knowledge translation. The On TRACK CRE will also increase Indigenous research capacity through training and employment of Indigenous Research Officers who will be involved in data collection, research analysis, publication writing and dissemination of research findings back to community and the wider sector. Indigenous Research Officers and IRG members will be co-authors in peer-reviewed publications and, where possible, co-presenters at national and international conferences. This will ensure cultural safety and the prioritisation of Indigenous values and perspectives in interpretation of study findings and their translation into clinical practice.

### Data for harmonisation

#### Dementia diagnosis

Diagnoses in each of the studies were based on data obtained through comprehensive medical assessment inclusive of medical, behavioural, neurological, cognitive and collateral caregiver measures performed by a trained specialist (geriatrician, older person psychiatrists, general physician) in dementia assessment. De-identified data from clinical assessments were reviewed by a panel of specialists to obtain consensus diagnoses based on the Diagnostic and Statistical Manual for Mental Disorders, 4th Edition (DSM IV-TR) [24]. Dementia subtypes of Alzheimer’s, vascular, mixed, or other were specified where possible. For the purpose of analyses, participants were reclassified based on DSM IV-TR diagnoses as having normal cognition, dementia, MCI [2] or CIND [8, 12]. The CIND and MCI groups demonstrated a decrement in cognitive functioning that met DSM-IV-TR criteria for a cognitive or amnestic disorder that was not attributable to a psychiatric illness or intellectual disability, but without significant loss in activities of daily living (ADL). For the harmonised dataset, MCI diagnoses in the KGOWS cohort were reclassified as CIND based on DSM IV-TR diagnoses in line with the other cohorts for analyses. Dementia subtypes of Alzheimer’s, vascular, mixed, or other were specified where possible based on the DSM IV-TR.

#### Variables of interest

Risk and protective variables of interest associated with dementia are derived from the 2020 Lancet report, the World Health Organisation (WHO) guidelines, Cardiovascular Risk Factors Aging, and Incidence of Dementia (CAIDE) index, and Australian National University Alzheimer’s Disease Risk Index (ANU-ADRI) and summarised in Table 2. These are life-course risk and protective factors for dementia in the general population and well established in the literature [13, 25–27]. We have included these measures for analysis across the three studies to establish whether the same risk factors are relevant to Aboriginal and Torres Strait peoples. Studies have also shown that certain syndromes such as falls, executive dysfunction, depressive symptoms and urinary incontinence may be more common in older people with cerebral white matter changes suggestive of cognitive vulnerability and impairment [28, 29]. Measures of mobility impairment, falls, sleep disturbance, urinary incontinence, and impairments in ADLs will be included to look at these syndromes. Additionally, history of cardiovascular, renal, or cerebrovascular disease inclusive of stroke or a transient ischaemic attack are included as markers of vascular comorbid conditions.

**Table 2 Tab2:** Compilation of risk factors of interest based on existing literature

Measure	Data available
Less education (< 10 years) *†‡§	Simple measure in KHAP W1. Levels of education available in KHAP W2, KGOWS and TSDPS.
Hearing impairment*	Yes
Physical inactivity/exercise *†§	Simple measure available in KGOWS but not in KHAP or TSDPS
Cognitive stimulation †§	Skilled work/jobs as a proxy measure in KGOWS only
Head injury with loss of consciousness *§	Yes
Diabetes †*§	Yes
Hyperlipidaemia/ high cholesterol †‡	KHAP W2, KGOWS and TSDPS only
Hypertension *†‡	Yes
Infrequent social contact/social isolation *†§	Only available from KGOWS data Subjective loneliness, living alone, social activity participation in prior 3 months for 10 activities
Diet (e.g. fish intake) †§	No
Alcohol consumption *†§	Yes
Air pollution *	No
Smoking *†§	Yes
Obesity (Body mass index > 30) †*‡	Only in KHAP W2 and KGOWS
Depression/Depressive symptoms *†§	Yes
Older Age ‡§	Yes
Sex §	Yes

* Dementia prevention, intervention, and care: 2020 report of the *Lancet* Commission [26]

†World Health Organisation (WHO) guidelines [30]

‡ Cardiovascular Risk Factors Aging, and Incidence of Dementia (CAIDE) Risk Score [31]

§ Australian National University Alzheimer’s Disease Risk Index (ANU-ADRI) [32]

Note: alcohol consumption is a protective factor in the ANU-ADRI but excessive alcohol consumption (> 21 units per week) is a risk factor in the Lancet 2020 Commission Report and in the WHO guidelines

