Three landmark Australian studies involving Aboriginal and Torres Strait Islander cohorts from Western Australia (WA), New South Wales (NSW), and the Torres Strait in Far North Queensland have researched factors associated with dementia. In a cross-sectional study of 363 Aboriginal people aged 45 years and older living in the remote Kimberley region of WA, dementia was associated with smoking, stroke, epilepsy, head trauma, poor mobility, incontinence and falls, after adjustment for age, sex and education. On follow-up, only age and head trauma endured as longitudinal risk factors for cognitive decline [8, 9]. In a cohort of 336 participants in the major city of Sydney and regional NSW, multivariable analysis highlighted age, childhood trauma, unskilled work, stroke and head injury as independent predictors of all-cause dementia alongside comorbid factors such as depression, current high risk alcohol use, low Body Mass Index (BMI), mobility impairment, functional impairment, incontinence, hospitalization in the past year, residing in residential care, social isolation and low physical activity levels [2, 10]. Older age, male sex, unskilled work history, and polypharmacy were associated with incident dementia and Mild Cognitive Impairment (MCI) [11]. On follow-up, age, male sex, unskilled work, polypharmacy and Apolipoprotein E allele 4 (APOE ε4) were longitudinal risk factors for cognitive decline. However, similar to the Kimberley study, the competing risk of mortality was not taken into consideration, which likely impacted these longitudinal results [9]. In the Torres Strait, cerebrovascular disease, chronic kidney disease, and older age were significantly associated with dementia in a cohort of 274 participants [12]. Vascular risk factors other than stroke, such as diabetes and hypertension, were not associated with dementia in any of the cohorts, possibly due to the ubiquity of these conditions, non-linear risk relationships or limited statistical power. This is consistent with the findings of a recent systematic review that highlighted the limited data on risk factors for vascular dementia and a lack of geographical representation for many risk factors for dementia [13].

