Wave 1 (W1) 2010–2012 [2, 14, 19]	Urban & Regional NSW	≥ 60	336	249 with normal cognition; 45 with dementia; 38 with MCI†; 4 with other cognitive disorder.
Wave 2 (W2) 2016–2018 [20]	Urban & Regional NSW	≥ 60	233‡	Of 336 W1 participants, 165 were followed-up, 68 had died and 103 did not participate. W2 cohort: 105 with normal cognition; 10 with dementia at baseline; 16 with incident dementia; 34 with MCI; 68 had died.
Torres Strait Dementia Prevalence Study (TSDPS)				
Wave 1 (W1) 2015–2018 [3, 12]	Torres Strait	≥ 45	274	175 with normal cognition; 39 dementia; 60 CIND.

CIND = Cognitive Impairment No Dementia; MCI = Mild Cognitive Impairment; NSW = New South Wales; WA = Western Australia

*CIND is defined as those with a decrement in cognitive functioning that met DSM-IV-TR criteria for a cognitive or amnestic disorder but without significant loss in activities of daily living (ADL) and not attributable to a psychiatric illness or intellectual disability

† MCI diagnoses in the KGOW cohort were reclassified as CIND based on DSM IV-TR diagnoses in line with the other cohorts for analyses

‡ Sample sizes include those who have died

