#### Data analyses

Data will be analysed using the Stata statistical package (StataCorp, College Station, Texas), version 17. Analyses will be performed on harmonised cross-sectional and longitudinal data. Associations between risk and protective factors of interest and the presence of dementia and/or cognitive impairment based on consensus diagnoses will be evaluated by univariable and multivariable binary logistic regression. Analyses by dementia subtype will also be conducted to ascertain risk factors of importance between groups. In the longitudinal cohort, risk factors of interest will be determined from baseline measures (W1), compared with consensus diagnoses at follow-up (wave 2) and analysed in relation to outcome measures of incident dementia and/or cognitive impairment using univariable and multivariable logistic regression. To account for the competing interest of death (*n* = 177 before wave 2 follow-up), multinominal logistic regression will be used to estimate the association between variables of interest and the following outcomes: (1) neither cognitive impairment nor dementia nor died; (2) cognitive impairment or dementia during the study; and (3) death between baseline and follow-up. Results will be reported as odds ratios (OR) with 95% confidence intervals (95% CI). Multivariable binary logistic regression will be used to adjust for the effect of confounding variables that are anticipated to be associated with dementia such as age, sex, education and study cohort. Variables that are significant in univariable analyses will be entered into a multivariable model, after which a process of clinical judgement and examination of measures including the Akaike and Bayesian information criteria will be employed to decide which variables to retain in the final multivariable model.

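### ADL impairment is a candidate predictor in the cross-sectional dementia models, although ADL status is what separates dementia from CIND

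*Protocol article*

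**What the plan says.** Under Variables of interest, after the risk factors of Table 2, the protocol article adds a group of markers: "Measures of mobility impairment, falls, sleep disturbance, urinary incontinence, and impairments in ADLs will be included to look at these syndromes".

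The outcome is a panel diagnosis. Under Dementia diagnosis: "De-identified data from clinical assessments were reviewed by a panel of specialists to obtain consensus diagnoses". The footnote to Table 1 (section Design) defines CIND as a cognitive decrement "but without significant loss in activities of daily living (ADL) and not attributable to a psychiatric illness or intellectual disability". The Dementia diagnosis section applies the same ADL criterion to CIND and MCI.

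Under Data analyses, associations with the "presence of dementia and/or cognitive impairment based on consensus diagnoses will be evaluated by univariable and multivariable binary logistic regression", and analyses by dementia subtype are planned. One route into the final model is given: "Variables that are significant in univariable analyses will be entered into a multivariable model". After that, "a process of clinical judgement and examination of measures including the Akaike and Bayesian information criteria will be employed" to choose what stays. No other analysis is set out for the ADL measure, and the limitations in the Discussion do not mention its overlap with the diagnosis.

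**The concern.** ADL loss appears on both sides of the regression. The panel judged function when it separated CIND from dementia, and the model would then use function to predict that judgement. Such a variable is almost certain to be significant on its own and to improve AIC and BIC greatly, so only an unspecified exercise of clinical judgement could take it out.

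Two things are at stake for the primary aim of finding risk and protective factors. First, a large ADL odds ratio could be read as a finding about risk when it largely restates the diagnostic rule. Second, the other factors are estimated conditional on ADL. If a factor such as stroke or head injury causes disability in its own right, conditioning on ADL pulls its odds ratio for dementia down. If it does not, its interval still widens. The Background offers limited power as one possible reason why vascular factors other than stroke were not associated with dementia in the single cohorts, so lost precision matters here.

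**Working it through.** **1. The plan's own figures.** From Table 1, the cross-sectional set is KHAP wave 2 (226 + 29 + 33 = 288 with a diagnosis), KGOWS wave 1 (336) and TSDPS (274): 288 + 336 + 274 = 898. Dementia: 29 + 45 + 39 = 113. CIND/MCI: 33 + 38 + 60 = 131. Together 244, and 244/898 = 27.2%. Both stated figures, 898 and 244 (27%), reproduce.

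**2. Where ADL defines the outcome.**
- Dementia versus CIND, or versus everyone else: ADL status is part of the dividing line.
- Dementia and CIND combined versus normal: 131 of the 244 cases (54%) have no significant ADL loss by definition, and 113 (46%) have dementia. ADL does not set this boundary, but it is still a likely consequence of being one of the 113.
- Longitudinal: the Abstract excludes people with dementia or impairment at baseline, and predictors are baseline values. ADL at that point is not part of the later diagnosis.

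**3. Size, on assumed inputs.** Assumptions: a factor with 15% prevalence (stroke-like); odds ratio 3 for CIND and for dementia, each against normal; measured ADL impairment in 70–90% of those with dementia and 10–20% of the others (unexposed); the factor multiplies the odds of ADL impairment by k = 1 or 2 in every class. The four KGOWS participants with another cognitive disorder are counted as unimpaired (898 − 244 = 654).

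*Odds ratio without ADL.* Let c and d be the odds of CIND and of dementia against normal in the unexposed, and t = c + d. Solving 0.85/(1 + t) + 0.15/(1 + 3t) = 654/898 gives t = 0.307, so c = 0.307 × 131/244 = 0.165 and d = 0.142. For dementia versus the rest, OR = 3(1 + c)/(1 + 3c) = 3 × 1.165/1.495 = 2.34. It is below 3 because the comparison group contains CIND. For the combined outcome it is 3.00.

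*Odds ratio with ADL, dementia versus the rest.* Multiply 2.34 by the exposed-to-unexposed ratio of P(no ADL loss) in dementia, divided by the same ratio in the others. For 80%/20% and k = 2, the odds of ADL loss go from 4 to 8 in dementia, so P(none) goes from 0.200 to 0.111 (ratio 0.556). In the others they go from 0.25 to 0.5, so P(none) goes from 0.800 to 0.667 (ratio 0.833). Then 2.34 × 0.556/0.833 = 1.56.

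*ADL's own odds ratio* for dementia versus the rest: (0.8/0.2)/(0.2/0.8) = 16 for 80%/20%; likewise 81 for 90%/10% and 9.3 for 70%/20%.

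Fitting the logistic models to the expected cell counts for 898 people gives:

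| ADL loss: dementia / others | k | Factor OR, dementia vs rest | SE rise | Factor OR, combined | SE rise |
|---|---|---|---|---|---|
| 90% / 10% | 2 | 2.34 → 1.35 | 34% | 3.00 → 2.53 | 11% |
| 80% / 20% | 2 | 2.34 → 1.56 | 13% | 3.00 → 2.54 | 5% |
| 70% / 20% | 2 | 2.34 → 1.65 | 10% | 3.00 → 2.58 | 4% |
| 90% / 10% | 1 | 2.34 → 2.34 | 45% | 3.00 → 3.00 | 10% |
| 80% / 20% | 1 | 2.34 → 2.34 | 16% | 3.00 → 3.00 | 5% |
| 70% / 20% | 1 | 2.34 → 2.34 | 11% | 3.00 → 3.00 | 3% |

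Adding ADL improves BIC by 100–304 in the dementia model and 36–125 in the combined model, after a penalty of ln 898 = 6.8. In the combined model the ADL odds ratio is 2.9–8.0.

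**4. A second illustration.** A simulation of 898 people (600 runs per scenario) used a factor with 30% prevalence and odds ratio 2, with ADL loss in 80–95% of dementia and 5–20% of others. For dementia versus the rest, the factor was significant in 76–81% of runs without ADL. With ADL added, this fell to 48–67% when the factor had no separate effect on ADL. It fell to 6–17% when the factor doubled the odds of ADL loss in people without dementia.

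**The case against.** The strongest reply is that ADL's place in the final risk-factor model is inferred. Table 2 does not list it. The text brings it in to study syndromes, and clinical judgement is part of the retention rule. The article also points to an appendix for variable details and to a registered analysis plan, neither of which is at hand, and ADL may be handled separately there. This is fair as to the final model. As to entry, the article itself names ADL among the variables of interest and states an entry rule with no exception, so the conflict lies in the text shown.

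Three stronger readings are tempting, and the documents do not support them:

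- *That the ADL odds ratio is true by definition.* The ADL criterion is written for CIND/MCI only. That dementia carries ADL loss follows by contrast and is not stated, and a measured ADL score need not equal the panel's judgement. Close to a component of the outcome is as far as the text goes.
- *That every model is circular.* The combined outcome is affected less, and the longitudinal analysis is not circular by definition.
- *That incontinence, mobility and falls should go too.* They may follow from dementia, but they are not in its stated definition. Keeping or moving them is a modelling preference, and the Discussion already says causality cannot be inferred from the cross-sectional data. The Background's summary of KGOWS, which lists functional impairment and other conditions "alongside comorbid factors such as depression", does not show that these were modelled apart.

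**Conclusion.** The concern holds for the cross-sectional models, most clearly with dementia or a dementia subtype as outcome. As written, ADL impairment would enter those models, would be strongly favoured by AIC/BIC under every scenario tried, and would carry an odds ratio that says little about risk.

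The effect on other factors depends on inputs the article does not give: ADL frequency by diagnosis, and whether the factor itself causes disability. Under the main assumptions above, a factor that also doubles the odds of ADL loss goes from 2.34 to 1.35–1.65 for dementia and from 3.00 to 2.53–2.58 for the combined outcome. If it has no such effect there is no bias, only a standard error 11–45% larger for dementia and 3–10% larger for the combined outcome. A reader might infer that attenuation is certain, but it is conditional. Some loss, of accuracy or of precision, occurred in every scenario tried.

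**What to change.** State under Variables of interest and Data analyses that ADL impairment is not a candidate predictor in the cross-sectional multivariable risk-factor models for dementia, dementia subtype, or dementia and CIND combined. Report it descriptively by diagnostic group (normal, CIND, dementia) instead. The combined outcome is included because ADL loss still follows from the dementia that makes up 46% of its cases.

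Baseline ADL may remain in the longitudinal analysis of people free of impairment at baseline, labelled as a possible early marker. The treatment of incontinence, mobility and falls need not change on this ground.

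The change is one of wording and needs no new data. The cost is a final model with fewer variables and a lower apparent fit.
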